#### Recruitment, participant timeline, and randomisation

The results of the pilot study preceding this full-size RCT ([name], [name], [name]: Unpublished observations) indicated that the recruitment procedure described in the original protocol for the senior meetings [24] needed to be adjusted to be more effective. Therefore, a plan consisting of three waves of recruitment strategies was adopted. The waves are hierarchical and an appropriate wave was to be added if an antecedent wave was unsuccessful in reaching the target number for inclusion. The first wave implies that participants are drawn at random from official registers in the urban district. All addresses, equally divided between the populations (Finland and the four countries in the Balkan Peninsula), are listed in random order (two separate lists). Based on the sampling lists, participants will be consecutively included in the study until the decided sample size is reached (n≥65 from each population). Letters will be sent to all randomly selected persons asking them to participate in the study. Invited participants also receive a description of the study, how it is to be conducted, and what is expected of those consenting to participate. The letter stresses the fact that participation is voluntary; it is followed by a telephone call about 1–2 weeks later. If no telephone number is to be found in public records, a second letter with a request to make contact by telephone is sent. During the call, the persons will be informed verbally about the study and given the opportunity to ask questions if anything is unclear. They are also asked personally if they would like to participate, while again stressing that participation is voluntary. Everyone who fulfils the criteria for inclusion and decides to participate is randomised by the research assistant after baseline assessment to one of the two groups using sealed, opaque envelopes prepared by an unattached researcher. Participants living together in the same household are allocated to the same group. Wave two is identical to wave one but involves an expansion of the targeted area to also include another adjacent urban district with similar demographics. Finally, wave three entails word-of-mouth promotion through one-chain snowballing [44]. This strategy uses former study participants and key persons in the aforementioned reference groups to facilitate spreading information about the study. Interested persons fulfilling inclusion criteria are invited to contact the operative group for further information and to undergo baseline assessment when appropriate. The third wave also includes local radio station advertisements containing brief information in the participants’ mother tongue on the study and how to contact the operative group. A detailed overview of the planned flow of participants is provided in Figure 1.

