#### Power calculation

The power calculation was based on results gained in the preceding study ‘Elderly Persons in the Risk Zone’ [24], using the Berg balance scale as a basis. The Berg balance scale is one of the secondary outcome variables (range 0–56), with assumed mean values for the intervention and control groups of 32 and 28, respectively (15% difference), and a standard deviation of 8 in both groups. To be able to detect a significant difference between the two groups in a two-sided test with a significance level of 0.05 and 80% power, we need at least 65 persons in each group. Therefore, a total of at least 130 persons will be included.

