#### Data management

All participant information, including informed consent forms, interviews on audio files, etc., will be stored separately from study records identified by code number in locked file cabinets in areas with limited access. The original data collection forms are to be stored in numerical order in a secure and accessible place and manner for a period of 10 years after completion of the study. An external research assistant will enter data into the computer and also perform quality control of the database. During and after the study completion, the research group will have access to the full database. Any modifications to data written to the database will be documented in a log book linked to the database. Regular back-ups of the database will be undertaken automatically by the university’s information technology department. The main database, as well as local databases, will be secured with password-protected access systems.

No data monitoring committee will be needed since risks in connection with this study are minimal, there is a fixed target figure for included participants, and no interim analyses are planned. Even so, the research group, and ultimately the research leader, will be responsible for database security and quality.

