#### Statistical analyses

Analyses of intervention outcomes and change over time will be made on the basis of the intention-to-treat principle, which means that participants will be analysed on the basis of the group to which they were randomised [45]. Standard adjustment of analyses according to eventual differences between groups at baseline will be made if necessary. After a thorough examination of the characteristics of collected data, the research group will consider different options for handling missing data. One possibility is the imputation method used in the preceding study ‘Elderly Persons in the Risk Zone’ [25,26], where a missing value was imputed with a value based on the median change of deterioration (MCD) between two measuring points (baseline and respective follow-up) of all those who participated at both measuring points. However, other methods of handling missing data will also be considered, and a final decision will be made by the lead researcher in consultation with a renowned statistician. Regardless of the method chosen, sensitivity analyses will be performed to compare the results to complete case analyses [46]. Although it is desirable, no subgroup analyses are predetermined. Instead, a valuation of the quality of collected data will determine if and which of these analyses are possible. Both descriptive and analytical statistics will be used to compare the groups and to measure change over time. Non-parametric statistics will be used in all cases where ordinal data are to be analysed; otherwise, parametric statistics will be used. A *p-*value of 0.05 or less will be considered significant. Statistical analyses will be performed using IBM SPSS Statistics for Windows, Version 22.0 (Armonk, NY, USA: IBM Corp. Released 2013).

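### The choice of subgroups is left until after data collection, on an undefined quality judgement in an open trial, with one unqualified 0.05 threshold, so the subgroup false-positive rate has no bound

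*Protocol article*

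**What the plan says.** The Statistical analyses section of the Protocol article deals with subgroups in two sentences. The first is "Although it is desirable, no subgroup analyses are predetermined". The second puts a rule in place of pre-specification: "a valuation of the quality of collected data will determine if and which of these analyses are possible". The same section gives one general threshold, under which a p "value of 0.05 or less will be considered significant". It makes no separate provision for subgroup results.

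Three other places bear on the point:

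- Table 2 gives the masking as non-blind, and the Masking section says that participants, professionals and assessors are all unblinded.
- Under Data management, "During and after the study completion, the research group will have access to the full database".
- Under Recruitment, participant timeline, and randomisation, sampling runs from two separate lists, one for Finland and one for the four Balkan countries, and "participants will be consecutively included in the study until the decided sample size is reached (n≥65 from each population".

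**The concern.** This is a stated rule, not silence. Subgroup analyses are wanted, and both whether to run them and which to run are settled after the data are in. The criterion has no definition or cut-off, so it constrains the choice very little. Because the trial is open and the research group can see the full database, the choice could be made by people who know the outcomes by arm.

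A statement that the programme helps some subgroup could then meet the same 0.05 standard as the main result, although the number of subgroups tried was never limited. A reader of the eventual report could not work out the error rate behind such a statement. Yet one factor needs no data to choose it: population of origin is built into the recruitment.

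**Working it through.** **1. The plan's own figure.** The article gives no subgroup error rate. Its only calculation is the sample size on the Berg balance scale: "assumed mean values for the intervention and control groups of 32 and 28, respectively (15% difference"), "a standard deviation of 8 in both groups", and a "two-sided test with a significance level of 0.05 and 80% power".

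- Normal approximation: n per arm = 2 × (1.960 + 0.842)² × 8² / 4² = 62.8, so 63.
- t-test: 63.8, so 64.
- Power at the stated 65 per arm: 81.3% (normal) or 80.8% (t-test).

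The stated 65 per arm (130 in total) therefore reproduces. There is no arithmetic error here, and these inputs can be used below.

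**2. False-positive subgroups.** The article gives no number of subgroups, so a range is assumed: one to five two-level factors, both levels tested at two-sided 0.05 on one outcome, no true effect, 130 people. If all tests were independent, the chance of at least one significant result with f factors would be 1 − 0.95^(2f). This is right for one factor, whose two levels do not overlap, and an upper guide for more. The simulated column uses normal outcomes, equal arms and random two-level factors in the same 130 people (40,000 trials per case), so it allows for the overlap.

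| Factors | Tests | Independence formula | Simulated, overlapping |
|---|---|---|---|
| 1 | 2 | 9.75% | 10.0% |
| 2 | 4 | 18.5% | 16.0% |
| 3 | 6 | 26.5% | 21.3% |
| 5 | 10 | 40.1% | 29.6% |

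A separate simulation of 4,000 trials per case gave 9.5%, 15.5%, 20.6% and 28.9%. The working range is therefore about 10% to 30%, or 2 to 6 times the nominal 5%. It covers one outcome at one time point.

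**3. Would interaction tests alone be enough?** With one interaction test per factor at 0.05, the rate is 1 − 0.95^f, which is 5%, 9.75%, 14.3% and 22.6% for one, two, three and five factors. This is lower, but it still grows with the number of factors. It stays at 5% only if a single factor is fixed in advance.

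**4. What the natural factor could show.** With 65 people per population and balanced allocation within each, there are about 32.5 per arm. On the Berg inputs:

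- Power within one population (t-test, standardised difference 4/8 = 0.5): 51%.
- If the true effect is the same in both populations, the chance that exactly one is significant is 2 × 0.51 × 0.49 = 50%. The chance that both are is 0.51² = 26%.
- Interaction test for a 4-point difference between the two population effects: SE = 8 × √(4/32.5) = 2.81, ratio 4/2.81 = 1.43 (1.425 unrounded), power = Φ(1.425 − 1.960) = 30%.

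These figures show why separate within-population p-values cannot establish a difference in effect, and how little the interaction test can detect. They apply to the Berg scale. The article gives no ADL inputs, so the corresponding ADL figures cannot be derived.

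**The case against.** The other side has a good case on several points, and most of it stands.

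- **The criterion is data quality.** On its face this is a feasibility check, such as completeness or group size. A reader might infer that subgroups will be picked on their results. The text does not say so; it only fails to rule it out.
- **Nobody is named as choosing.** A reader might infer that an unmasked research group makes the selection. In the Statistical analyses section that group is named for missing-data options, not for subgroups. What the documents support is that the trial is open and the group has the data.
- **No separate Finland and Balkan tests are planned.** A reader might expect a report that the programme works in one population and not the other. No passage plans this, and the two populations were chosen for practical reasons of language. The 50% figure is a warning about one way of reading such data, not a forecast of what the trial will do.
- **An analysis plan or full protocol may hold an exploratory label or an interaction test.** Their absence from an article is not the point. An analysis plan that fixed subgroups in advance would, however, depart from the rule stated here.
- **Nothing central is touched.** No hypothesis or research question concerns a subgroup, and saying that none is predetermined already tells readers that any such result is unplanned.

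What remains is the rule itself: an undefined, data-dependent choice of an unlimited number of subgroups, under a threshold with no exception for them.

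**Conclusion.** The point holds in a limited form. As written, the plan puts no bound on the false-positive rate among subgroup results. The size, about 10% to 30%, rests on an assumed one to five two-level factors, both levels tested, one outcome, normal data and no true effect. None of these assumptions comes from the article. More factors, outcomes or time points would raise the figure; a single interaction test on one pre-named factor would hold it at 5%.

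The primary comparison and the sample size are not affected. Severity is low to moderate: worth correcting because it is cheap and limits what may be concluded, but no threat to the main result.

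**What to change.** In the Statistical analyses section, replace the data-dependent rule with these statements:

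- Any planned subgroup is fixed before outcomes are examined by arm. Country-of-birth group (Finland versus Balkan) is the natural choice, since recruitment already aims for at least 65 from each.
- It is assessed by the arm-by-population interaction on ADL, with a method suited to an ordinal outcome, for example an ordinal regression model. The effect and its 95% confidence interval are shown in each population.
- Every other subgroup analysis is post hoc and exploratory, and supports no claim of effect.
- Separate within-subgroup p-values are not used to claim that effects differ.

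The cost is a few sentences and one extra analysis, with no new data. The section's rule that ordinal data get non-parametric statistics would need to allow for the interaction model. There are two drawbacks. The interaction test has low power (about 30% for a 4-point Berg difference between populations; unknown for ADL), so a non-significant result would not show equal effects. And unplanned subgroup results could no longer be presented as significant findings.

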### Design of the implementation study

#### Theoretical basis

The implementation in any given context can be seen as a dynamic process involving several phases. The knowledge-to-action model (KTA) [47] forms an overarching theoretical framework for the implementation process, which involves all stakeholders (i.e. researchers, decision-makers, and users) as they cooperatively transform an intervention into practice. The goal of the KTA model is to enhance health status through knowledge creation and action, both of which consist of ideal phases (Figure 2). The focus, as regards the aim of this study, is the action cycle (application), where the evidence-based senior meetings intervention is implemented into practice. In this practice, it is important to identify components that support or inhibit the implementation. To evaluate the impact in an implementation results in new knowledge, which can form a basis for creating useful and practically applicable strategies, tools, and products to be used in similar contexts in the future.

**Figure 2 Fig2:**
[figure not shown]
**The knowledge-to-action model [**
47
**].**

#### Study population

In addition to participants recruited for the RCT part of the study, members of the steering committee (five persons), the research group (nine persons), and the operative group (four persons) will be included in the population for the implementation study.

#### Data collection and analysis

Several aspects of the senior meeting implementation will be studied: the feasibility of the recruitment method; its effectiveness; hindrances at all levels (personal, professional, organisational); eventual adaptations of the recruitment method and intervention; and intervention fidelity. It is essential to report that even though the Promoting Aging Migrants’ Capabilities Study uses a predetermined intervention protocol, it entails possibilities for adaptation by answering to any contextual needs. For instance, the recruitment of participants will be closely monitored with openness to adaptation by the development of new strategies, as well as strategies for participant adherence to intervention and follow-ups. Any adaptation to the intervention protocol is decided, documented, and evaluated in collaboration with the operative group, research group, and steering committee at regular scheduled audits throughout the study. Further, an evaluation of whether the design and content of the senior meetings support self-change by participants will be conducted. As recommended for case studies, multiple sources of data collection will be used, thereby enabling triangulation [36]. Data will be collected throughout the study; methods include direct observations, qualitative interviews, questionnaires, and study documentation. Data analysis will be done in accordance with guidance given for each distinct data collection method, and thereafter aggregated for final results.

### Qualitative studies

In addition to the study of intervention effects and implementation output, it is important to find out how participants and personnel in the urban district experience different aspects of the health-promoting programme. This will be done using individual interviews. These interviews will give the respondents opportunities to highlight their priorities in their own way and may reveal ideas that are not anticipated by the researchers [48]. In addition, the complex factors that affect habits and ways of thinking about health in the context of migration will be illuminated.

#### Data collection and analysis

Individual interviews, which may be characterized as semi-structured ‘in-depth’ interviews, will be carried out with study participants and personnel in the urban district. The interviews aim to elicit the individual experiences and perceptions of participating in a person-centred and health-promoting intervention. We will consider the balance between male and female study participants. The interviews will be audio-taped, transcribed verbatim, and analysed, to identify patterns and themes in the statements [49,50]. The qualitative data will enable an analysis of similarities and differences between the perceptions and experiences of participants and personnel at both the individual and group level. Results of the qualitative studies may contribute important knowledge to the evaluation of the study as a whole.

### Ethical considerations

The ethical problems that may arise in the study primarily concern those who receive intervention versus those persons who receive conventional care. If the intervention proves effective and has a positive effect on the health and wellbeing of participants, then it will be offered to everyone in the study control group once the study has been completed. In addition, there is a risk of experiencing questions in the data collection form as tiring or bothersome, which was also addressed in the pilot study ([name], [name], [name]: Unpublished observations). Overall, the risk is small compared with the benefit that participants will gain from obtaining information and support (the intervention group) and regular assessment and discussion of their own capacity. Nevertheless, the researchers will be observant of signs that may indicate fatigue, and in such cases will make the visit short and return on a later occasion. If, however, a participant experiences substantial difficulties coping or has a temporary lack of motivation, and this becomes a threat to continued participation, a revised version of the data collection form with a few prioritised items will be offered as an alternative to the full version.

The risk of stigmatisation of persons born abroad and ethical dilemmas about dividing persons based on age and country of birth were carefully weighed against the importance of visualising inequities between different groups of people. Health and healthcare inequities due to age and migration status will never be bridged if researchers continue to exclude aging persons who are born abroad or who do not speak the dominant language. Regarding language, inclusion of persons who have a different mother tongue from the researchers requires specific ethical consideration. It is always important to ensure that everyone who participates is aware of what they consent to, and when dealing with linguistic differences, consideration must be given to linguistic preferences of participants. In the present study, all participants were able to choose the language they preferred to be addressed in. The Regional Ethical Review Board in Gothenburg approved this study (reference #821-11). The final approval document, as well as the informed consent form to be signed by participants, can be retrieved by contacting the first author (SG) or the last author ([name]).

### Study protocol amendments

Any modifications to the protocol that may impact the conduct of the study or potential benefit of the participant, including changes in study objectives, study design, population, sample sizes, study procedures, or significant administrative aspects, will require a formal amendment to the protocol. Such amendment will be agreed upon by the steering committee, and approved by the Regional Ethical Review Board in Gothenburg prior to implementation. Administrative changes to the protocol are minor corrections and/or clarifications that have no effect on the way the study is to be conducted. These administrative changes will be agreed upon by the steering committee, and will be documented in meeting records.

### Dissemination policy

Research articles with different focuses (e.g. the intervention outcome, the implementation output, and qualitative papers) will be submitted to relevant scientific journals. Individuals who fulfil authorship criteria should not remain hidden and should have authority over manuscript content. Similarly, those who do not fulfil such criteria should not be granted authorship. No professional writer will be employed in the writing of articles, but language validators will be engaged. The research findings are planned to be presented at appropriate national and international conferences. Information about results relevant to politicians, policy makers, and relevant personnel will be made at scheduled meetings. In addition, information for participants and the public will be given at public meetings in easily accessible premises in the targeted urban district, starting not later than 1 year after completion of the study. Popular science reports and summary research information in the participants’ mother tongue will also be compiled and made publically available.

For transparency, upon written request from recognized researchers in the field, the study’s lead researcher will consider sharing deidentified data. Such actions will be decided in line with the policy at the University of Gothenburg, and will be considered no later than 3 years after the collection of the 1-year post-randomisation interviews.

